### Radiotherapy-related assessment

Quantitative MR parameters (BOLD signals complimented by perfusion information from DCE-MRI and cellularity information from DWI-MRI) derived at various time points during treatment will be used to create a high-risk map that can be delineated and registered onto the anatomic sequences of the planning MRI performed at the time of image-guided brachytherapy. The map will be used to delineate a residual high-risk tumour volume (HTV-T_res_) within the high-risk clinical target volume (HR-CTV) for brachytherapy. Original treatment plans will then be reoptimised escalating the HTV-T_res_ to 140% of the original HR-CTV prescription (9.8 Gy/fraction) with the aim of achieving the volume of HTV-T_res_ receiving 140 Gy (HTV-T_res_V_140_) ≥90% and 98% of HTV-T_res_ to receive over 100 Gy (D_98_≥100 Gy) while maintaining HR-CTV coverage and organ-at-risk dose-volume histograms within tolerance.

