## Method

### Study design and setting

EMPIRIC (ClinicalTrials.gov NCT05532930) is a prospective, non-randomised, single-centre (Mount Vernon Cancer Centre, UK) observational study in which patients with locally advanced cervical cancer fit for CRT are included.

The study aims to recruit 40 patients in total over an accrual period of 36 months at Mount Vernon Cancer Centre, UK. The study started in August 2022 and is actively recruiting. It is a single cohort study, where patients undergoing CRT (45 Gy in 25# of external beam radiotherapy with concurrent weekly cisplatin, followed by image-guided brachytherapy boost) for cervical cancer undergo fMRI before, during and at the end of their treatment, along with analysis of CTC, CtDNA and tissue biopsies. Online supplemental table 1 provides an overview of the study schedule.

10.1136/bmjopen-2023-077390.supp1Supplementary data

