#### Secondary outcomes

To evaluate sensitivity and specificity quantitative parameters derived from DCE-MRI, DWI-MRI and BOLD-MRI as predictors of overall survival at 2 years in patients with locally advanced cervical cancer after CRT.To evaluate sensitivity and specificity quantitative parameters derived from DCE-MRI, DWI-MRI and BOLD-MRI as predictors of the TVRR in response to CRT of patients with locally advanced cervical cancer.To apply radiomics for derivation of textural imaging features as predictors of progression-free (local, nodal, systemic), overall survival and TVRR after CRT for cervix cancer.To correlate temporal changes in quantitative MRI parameters during CRT with molecular markers from tissue biopsies and CTCs isolated from peripheral blood samples.To explore the feasibility of using quantitative MRI parameters to provide a roadmap in identifying high-risk regions for potential dose escalation with radiotherapy.

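### The re-planning target for the residual high-risk volume is given as 140% of prescription (9.8 Gy/fraction) but its V140 coverage aim as 140 Gy: a probable unit inconsistency

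*Protocol article*

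**What the plan says.** The Radiotherapy-related assessment section of the protocol article describes a re-planning exercise. A map built from the functional MRI defines HTV-Tres inside the HR-CTV, and the original brachytherapy plans are re-optimised. One sentence gives three dose figures for HTV-Tres:

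- the escalation level: "escalating the HTV-T_res_ to 140% of the original HR-CTV prescription (9.8 Gy/fraction");
- a coverage aim: "with the aim of achieving the volume of HTV-T_res_ receiving 140 Gy (HTV-T_res_V_140_) ≥90" per cent;
- a near-minimum aim: "98% of HTV-T_res_ to receive over 100 Gy (D_98_≥100 Gy").

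HR-CTV coverage and organ-at-risk limits are to be kept. Study design and setting gives the treatment as "45 Gy in 25# of external beam radiotherapy with concurrent weekly cisplatin, followed by image-guided brachytherapy boost". The exercise serves the last of the Secondary outcomes: "To explore the feasibility of using quantitative MRI parameters to provide a roadmap in identifying high-risk regions for potential dose escalation with radiotherapy".

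The article does not give the number of brachytherapy fractions, the dose scale (physical, EQD2 or BED), the alpha/beta ratio, or whether external beam dose counts towards the 140 Gy and 100 Gy.

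**The concern.** The number 140 appears twice in one sentence, first as a percentage of the prescription per fraction and then as an absolute dose in gray. No conversion links the two. If the escalation level and the coverage aim describe the same plan, they should lead to about the same dose in HTV-Tres.

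If they do not, a planner has two targets. A plan built to 9.8 Gy/fraction could miss the V140 aim, while a plan built to 140 Gy could escalate well beyond 140% of prescription. Whether escalation is reported as achievable within organ-at-risk tolerance would then depend on which figure was followed. Future work foresees a randomised study of dose escalation at brachytherapy, so the level found feasible here may be carried forward.

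**Working it through.** **Inputs from the article.** External beam 45 Gy in 25 fractions, so 1.8 Gy/fraction (Study design and setting). Escalated dose 9.8 Gy/fraction, stated as 140% of the HR-CTV prescription; aims of 140 Gy to at least 90% of HTV-Tres and D98 of at least 100 Gy (Radiotherapy-related assessment).

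**Assumptions, not in the article.** n = 3 to 5 brachytherapy fractions, with 6 also shown; external beam included in the total; 9.8 Gy/fraction taken as the dose to 90% of HTV-Tres; alpha/beta 10, with 6 and 3 also shown.

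**Step 1: the article's own figure.** 9.8 / 1.4 = 7.0 Gy/fraction. The percentage and the dose per fraction agree with each other, and 9.8 Gy reads as the escalated dose.

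**Step 2: total dose at 9.8 Gy/fraction.** EQD2 = n x d x (d + alpha/beta) / (2 + alpha/beta). BED = n x d x (1 + d / (alpha/beta)).

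- EQD2, alpha/beta 10: external beam 45 x 11.8/12 = 44.25 Gy; each fraction 9.8 x 19.8/12 = 16.17 Gy.
- EQD2, alpha/beta 3: external beam 45 x 4.8/5 = 43.2 Gy; each fraction 9.8 x 12.8/5 = 25.09 Gy.
- Physical: 45 + 9.8n.
- BED, alpha/beta 10: external beam 45 x 1.18 = 53.1 Gy; each fraction 9.8 x 1.98 = 19.40 Gy.

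| Total (Gy) | n = 3 | n = 4 | n = 5 | n = 6 |
|---|---|---|---|---|
| EQD2, alpha/beta 10 | 92.8 | 108.9 | 125.1 | 141.3 |
| Physical | 74.4 | 84.2 | 94.0 | 103.8 |
| EQD2, alpha/beta 3 | 118.5 | 143.6 | 168.6 | 193.7 |
| BED, alpha/beta 10 | 111.3 | 130.7 | 150.1 | 169.5 |

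At alpha/beta 10 the EQD2 shortfall from 140 Gy is 47.2, 31.1 and 14.9 Gy for n = 3, 4 and 5. The EQD2 figures meet at (140 - 44.25)/16.17 = 5.92 fractions for alpha/beta 10 and (140 - 43.2)/25.09 = 3.86 for alpha/beta 3. At alpha/beta 6, five fractions give 140.7 Gy. In physical dose, (140 - 45)/9.8 = 9.7 fractions would be needed.

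**Step 3: what 140 Gy would require (EQD2, alpha/beta 10).** Solving 44.25 + n x d x (d + 10)/12 = 140 for d gives:

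| | n = 3 | n = 4 | n = 5 | n = 6 |
|---|---|---|---|---|
| Gy/fraction | 15.20 | 12.67 | 10.96 | 9.71 |
| % of 7 Gy | 217 | 181 | 157 | 139 |

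**Step 4: V140 read as a percentage.** If V140 is the volume receiving 140% of prescription, the aim becomes D90 of at least 9.8 Gy/fraction. That is the stated escalation exactly, whatever the fraction number or alpha/beta.

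**Step 5: the D98 aim.** With the same equation set to 100 Gy, D98 needs 10.75, 8.87 and 7.60 Gy/fraction for n = 3, 4 and 5, or 154%, 127% and 109% of prescription. With V140 as 140%, it is the tighter dose level for n = 4 and 5, as expected for a D90 beside a D98. For n = 3 the D98 aim already asks for more than 140%, so V140 would be redundant.

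**The case against.** The best defence is that a dose per fraction and a total dose cannot be compared until four things are supplied: fraction number, dose scale, alpha/beta and the treatment of external beam. The article gives none of them, and a condensed article may leave them to the full protocol. Some choices bring the figures close: EQD2 of 141.3 Gy at 6 fractions with alpha/beta 10, or 143.6 Gy at 4 with alpha/beta 3. On BED with alpha/beta 10, 140 Gy lies between the totals for 4 and 5 fractions (130.7 and 150.1 Gy). Taking 9.8 Gy as the dose to 90% of the volume is also an assumption. If it is only a floor, a plan reaching 140 Gy satisfies both figures. The D98 aim is also in gray, so 140 Gy may be deliberate.

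Most of this stands, and it limits the claim. A reader might infer that the sentence is proven to contradict itself, or that 140 Gy is certainly a misprint for 140%. The article supports neither: agreement is possible under conventions it does not exclude, and the percentage reading fits poorly with the D98 aim at 3 fractions. If 9.8 Gy were the original prescription, 140% would be 13.72 Gy/fraction and the totals at alpha/beta 10 would be 125.6, 152.7 and 179.8 Gy EQD2 for n = 3, 4 and 5. The exact 1.4 x 7 makes that reading unlikely.

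The defence does not remove the point. The fault is not the missing fraction number or convention. Two stated figures sit side by side without a link, and over 3 to 5 fractions they disagree both in physical dose and in EQD2 at alpha/beta 10.

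**Conclusion.** The concern holds as a probable unit inconsistency. It rests on external beam being included and on 9.8 Gy/fraction being the dose to 90% of HTV-Tres. With 3 to 5 fractions, the stated escalation then falls about 15 to 47 Gy short of the 140 Gy aim in EQD2 at alpha/beta 10, and further short in physical dose. At 4 fractions on that EQD2 scale, the choice of figure means testing 140% or 181% of prescription. Which figure is wrong cannot be told from the article.

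The severity is minor. A reader might infer that patients could receive the wrong dose or that the trial's main results are at risk, but the text describes re-optimisation of original plans for a feasibility objective, with planning aims and not pass/fail criteria. The primary outcome, the sample size and the regression analyses do not use these figures.

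**What to change.** Correct the one sentence so that its figures agree, in one of two ways:

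1. If a percentage was meant, define HTV-Tres V140 as the volume receiving 140% of the HR-CTV prescription (9.8 Gy/fraction). Confirm at the same time whether the D98 aim of 100 is in gray or in per cent of prescription.
2. If 140 Gy was meant, state the dose convention (physical, EQD2 or BED, the alpha/beta used, and whether external beam is included), and restate the escalation percentage and dose per fraction to match.

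The cost is one corrected sentence. Any re-planning already done should be checked for which figure it followed before feasibility is reported.

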### Follow-up schedule

All patients from this study will be followed up at 3 months, 6 months, 12 months and then yearly as outlined in table 2. Treatment outcome data will be collected for all patients until 2 years post-CRT end date.

**Table 2 T2:** Post-treatment follow-up and imaging schedule as per standard of care

Months	1	3	6	12	24
Clinical assessment*	^✓^	^✓^	^✓^	^✓^	^✓^
MR RECIST assessment		^✓^		^✓^	^✓^

^✓^ Indicates when patient will receive stated treatment or undergo stated investigation.

* All post-treatment imaging follow up procedures (including Positron Emission Tomography (PET)/CT and MRI scanning) are carried out per standard of care at Mount Vernon Cancer Centre.

RECIST, Response Evaluation Criteria in Solid Tumours.

Objective tumour response on MR in patients with measurable disease will be assessed by RECIST V.1.1 week 2 of CRT (fraction 10), week 5 of CRT prior to brachytherapy (fraction 25) and 3 months post the end date of CRT.

Progression-free survival (local, nodal, distant) and overall survival at 1 and 2 years will be measured. The study will close once the final patient accrued has completed a 2-year follow-up.

### Outcomes

#### Primary outcome

To evaluate sensitivity and specificity of quantitative parameters derived from DCE-MRI, DWI-MRI and BOLD-MRI as predictors of progression-free (local, nodal, systemic) survival at 2 years post-treatment in patients with locally advanced cervical cancer after CRT.

#### Secondary outcomes

To evaluate sensitivity and specificity quantitative parameters derived from DCE-MRI, DWI-MRI and BOLD-MRI as predictors of overall survival at 2 years in patients with locally advanced cervical cancer after CRT.To evaluate sensitivity and specificity quantitative parameters derived from DCE-MRI, DWI-MRI and BOLD-MRI as predictors of the TVRR in response to CRT of patients with locally advanced cervical cancer.To apply radiomics for derivation of textural imaging features as predictors of progression-free (local, nodal, systemic), overall survival and TVRR after CRT for cervix cancer.To correlate temporal changes in quantitative MRI parameters during CRT with molecular markers from tissue biopsies and CTCs isolated from peripheral blood samples.To explore the feasibility of using quantitative MRI parameters to provide a roadmap in identifying high-risk regions for potential dose escalation with radiotherapy.

### Sample size and power

In the absence of evidence in published literature on which to derive sample size calculations in the context of an exploratory feasibility study, formal statistical power calculations have not been performed. An aim of exploratory studies is to determine feasibility of specific study aspects, subsequently allowing for estimation of sample sizes in the future studies.

The proposed sample size of 40 patients is a convenience-based sampling reflecting the annual estimate of patients with locally advanced cervical cancer likely to be eligible for this study at Mount Vernon Cancer Centre. From January 2019 to December 2019, there were a total of 30 patients with locally advanced cervical cancer treated with radical CRT. Assuming a conservative patient decline/withdrawal rate of 30%, the estimated annual number of complete study accruals is 21. This should enable a total number of 40 patients to be recruited over a period of 24 months. In a mixed population of cervix patients, a 2-year recurrence rate (local, nodal and distant) of 35% is assumed resulting in an estimated number of 14 events by the end of the study period.

### Data handling and record keeping

All study data will be securely held and managed in accordance with relevant statutory data protection legislation. Technical appendix, statistical code and dataset will be stored and accessible through a local server. Information about study subjects will be kept confidential and managed according to Trust policies. Patients will be assigned an individual study ID number, which will be applied to all study documentation.

The study case report form will be used to capture the data required including eligibility, demographics, standard of care treatment data, follow-up data from medical records and routine clinical assessment.

Pseudonymised image data and extracted parameters will be transferred to a dedicated password-protected laptop or PC held by the chief investigator for analysis by the chief investigator or delegated individual.

### Records retention

Archiving for this study will be carried out according to the sponsor’s research standard operating procedure, gSOP-17. Destruction of essential documents will require authorisation from the sponsor. Archiving will be authorised by the sponsor following submission of the end-of-study report MRI source data will be stored and archived as per the Trust’s standard arrangements for patient’s medical records. MRI data and any related electronic and/or paper reports will be stored in line with the Trust’s standard arrangements for retention periods for patient medical records and standard UK policy, this is, at least 25 years subject to media being readable. Essential documents will be archived for 5 years after completion of the study.

### Statistical analysis

Using logistic and Cox regression models the study will evaluate:

Different thresholds and temporal changes of fMRI parameters (DCE-MRI, DWI-MRI and BOLD-MRI) at various time points during cervical CRT can predict progression-free (local, nodal, distant) survival.Different thresholds and temporal changes of fMRI parameters (DCE-MRI, DWI-MRI and BOLD-MRI) at various time points during cervical CRT can predict response to treatment as defined by TVRR.Different thresholds and temporal changes of fMRI parameters (DCE-MRI, DWI-MRI and BOLD-MRI) at various time points during cervical CRT can predict overall survival.Different radiomics features can predict response to cervical CRT in terms of TVRR, progression-free (local, nodal, distant) survival and overall survival.Different thresholds and temporal changes of fMRI parameters (DCE-MRI, DWI-MRI and BOLD-MRI) at various time points during cervical CRT can predict changes in immunohistochemical markers of hypoxia and epithelial mesenchymal transition.

For each of the above regression analyses, a univariate logistic regression reporting the OR with 95% CI and p value from the likelihood ratio test will be performed. All covariates (fMRI parameters and radiomic features in table 1) and demographics) with a p<0.1 will be entered into a multivariate, forward conditional logistic regression and subsequently a p<0.05 will be considered statistically significant. The utility of the final prognostic model will be evaluated using sensitivity, specificity and area under the receiver operating characteristic curve.

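### Evaluating several unspecified thresholds per continuous fMRI parameter on about 14 events would inflate screening and overstate the primary sensitivity and specificity if the best cut is kept

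*Protocol article*

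**What the plan says.** The primary outcome (protocol article, Primary outcome) is "To evaluate sensitivity and specificity of quantitative parameters derived from DCE-MRI, DWI-MRI and BOLD-MRI as predictors of progression-free" survival at 2 years. The first objective under Statistical analysis is to assess, with logistic and Cox models, whether "Different thresholds and temporal changes of fMRI parameters (DCE-MRI, DWI-MRI and BOLD-MRI) at various time points during cervical CRT can predict progression-free" survival. The same wording about thresholds recurs for tumour volume reduction, overall survival and tissue markers.

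The DCE, DWI and BOLD measures in Table 1 (V_e, K^trans, k_ep, v_p, ADC, R2*) are all continuous, and scans are taken at three time points.

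The analysis runs in three steps. Each covariate gets a univariate logistic model with a likelihood ratio test. Covariates with p<0.1 go into forward selection, where p<0.05 counts as significant. The final model is then judged by sensitivity, specificity and area under the ROC curve. The section names no separate sample for that last step. The Future work section places validation in a later, larger study.

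On size, Sample size and power states that "The proposed sample size of 40 patients is a convenience-based sampling", that "a 2-year recurrence rate (local, nodal and distant) of 35% is assumed", which it translates into 14 expected events, and that "formal statistical power calculations have not been performed".

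**The concern.** A threshold has to be imposed on a continuous parameter. When several are tried and the one that best separates patients with and without progression is kept, the p value no longer has its nominal meaning. Sensitivity and specificity at that cut, read off in the same patients, are also too high on average. The problem sits inside each single parameter, so correcting for the number of parameters or dropping forward selection would leave it in place. Dichotomising also discards information, which 14 events can ill afford.

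What is at stake is the primary result itself, because it is expressed as sensitivity and specificity. The article also intends this study to inform later sample sizes, a validation study and then a randomised dose-escalation study. Optimistic accuracy could carry the wrong parameters forward and make those studies too small.

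**Working it through.** **The plan's own figures.** Events: 40 x 0.35 = 14, so 14 events and 26 non-events, as stated. Accrual: 30 x 0.7 = 21 per year, or 42 in 24 months, consistent with the stated 40. There is no power figure to reproduce.

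**Assumptions.** The article gives neither the number of thresholds nor a selection rule. I therefore assume that the best cut is kept and vary how many are tried. The 2-year outcome is treated as complete and analysed by logistic regression; censoring and Cox models were not simulated.

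**False positives for one uninformative parameter.** Order the 40 patients by the parameter. A cut puts m patients on one side, k of them with events. With l(k,n) = k ln(k/n) + (n-k) ln(1-k/n), the likelihood ratio statistic is

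G = 2[l(k,m) + l(14-k,40-m) - l(14,40)],

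referred to chi-square on 1 df (critical values 3.84 for 0.05 and 2.71 for 0.1).

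A single median split (m = 20) can be checked exactly. k = 10 gives G = 4.05 (p = 0.044) and k = 9 gives G = 1.78 (p = 0.18). Rejection therefore needs a split of 10:4 or more extreme, at either level. Its probability is 2 x 1,112,140,680 / 23,206,929,840 = 0.096, where the denominator is C(40,14). So one fixed split already exceeds 5%, because the statistic is discrete at this size.

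For several cuts, 100,000 random allocations of 14 events among 40 patients were generated and the largest G kept (the continuous-term row used 10,000 simulated datasets):

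| Cuts tried | p<0.05 | p<0.1 |
|---|---|---|
| None (continuous term) | 5.5% | 11.0% |
| Median only | 9.6% | 9.6% |
| 4 quintile cuts | 11.8% | 30.1% |
| 3 cuts, near tertiles and median | 12.4% | 29.1% |
| 3 quartile cuts | 19.1% | 26.4% |
| All cuts, 25th-75th percentile | 29.0% | 44.8% |
| All cuts, 20th-80th percentile | 30.9% | 51.1% |
| All cuts, 10th-90th percentile | 44.4% | 70.7% |
| Every cut | 55.0% | 81.8% |

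Against the nominal 5%, three or four cuts inflate by 11.8/5 = 2.4 to 19.1/5 = 3.8 times, and a range search by 29.0/5 = 5.8 to 55.0/5 = 11 times. Against the 9.6% of a single median split, the factors are 11.8/9.6 = 1.2 to 19.1/9.6 = 2.0, and 29.0/9.6 = 3.0 to 55.0/9.6 = 5.7.

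**Optimism in sensitivity and specificity.** A normally distributed marker was drawn for 14 and 26 patients, 20,000 times. The cut maximising Youden's J = sensitivity + specificity - 1 was chosen between about the 10th and 90th percentiles. For the uninformative marker the direction was also left free. Apparent values are compared with the true values at the chosen cut:

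| True AUC | Apparent sens / spec | True sens / spec | Excess (points) | J apparent vs true |
|---|---|---|---|---|
| 0.50 | 0.654 / 0.612 | 0.481 / 0.519 | 17.3 / 9.3 | 0.27 vs 0.00 |
| 0.65 | 0.693 / 0.661 | 0.583 / 0.603 | 11.0 / 5.8 | 0.36 vs 0.19 |
| 0.70 | 0.721 / 0.696 | 0.617 / 0.640 | 10.4 / 5.6 | 0.42 vs 0.26 |

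**The case against.** The article does not say that a cut is chosen on outcome or that the best is kept. A few literature-based thresholds would fit the same sentence. A reader might infer that the plan commits to an exhaustive search, and quote 44% or 55% as its false-positive rate. The documents do not support that: those figures belong to one assumed way of carrying out the plan.

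The operative paragraph can also be read more kindly. Its covariates are the Table 1 quantities themselves, which could enter as continuous terms, and it attaches sensitivity, specificity and a threshold-free AUC to the final model. Cut-off rules and internal validation are details that an article may leave to a fuller document. The study is exploratory, sized by convenience, and defers validation.

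Much of this stands. The size has to be given as a range conditional on an assumption, part of the few-cut excess comes from the discrete test, and the silence on internal validation is not a fault in itself. What remains is the wording the article does contain: more than one threshold per parameter, uncorrected significance rules, and a primary outcome that asks for the sensitivity and specificity of the parameters in the same 40 patients. The p<0.1 screen offers no protection, since a few cuts already let an uninformative parameter through in more than a quarter of trials. Exploratory status excuses the missing power calculation but does not make a biased estimate unbiased.

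**Conclusion.** The concern holds in conditional form and is a should-fix. If the best of several cuts is kept, the false-positive rate for one uninformative parameter lies between about 12% and 55% at p<0.05, depending on how many cuts are tried. Several-fold inflation is a fair description for a search over a range, but with three or four cuts it is at most a doubling relative to one median split. The overstatement of 6-17 points applies to a search over the central 80% of values and would differ for other searches. All figures rest on 14 events in 40 patients and complete 2-year follow-up. It would go too far to say that the primary result will necessarily be inflated: a small set of cuts fixed without reference to outcome, all reported, would avoid the optimism. The article as written does not restrict the analysis to that.

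**What to change.** In Statistical analysis, replace the evaluation of various thresholds by entering each parameter, and its change over treatment, as a continuous term. In the simulation this brings the false-positive rate back to 5.5% and 11.0% at the two levels. Extend the AUC already planned for the final model to each parameter, and make it the headline accuracy measure.

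Sensitivity and specificity can stay as the stated primary outcome, reported in one of two ways:

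- At a cut fixed without reference to outcome, such as a literature value or the cohort median, with an exact test if the split is tested.
- At a cut derived from outcome, with the choice of cut repeated inside cross-validation or bootstrap, optimism-corrected values with confidence intervals, and the cut labelled hypothesis-generating.

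A criterion such as sensitivity at a set specificity belongs in the second group, because its cut is located from the patients without progression.

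The cost is a change of wording and minor programming, with no extra patients or scans. The reported accuracy will look less impressive.

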**Trial registration number:**

NCT05532930.

STRENGTHS AND LIMITATIONS OF THIS STUDYNovel imaging approach: Multiparametric functional MRI (fMRI) including T2, diffusion-weighed imaging, dynamic contrast-enhanced and blood oxygen level-dependent-MRI.Temporal data: fMRI obtained prior, during and at the end of chemoradiotherapy will capture longitudinal changes in tumour and fMRI-derived parameters.Parallel molecular analysis: Tissue and liquid biopsies (circulating tumour cells and circulating tumour DNA) will be collected and independently analysed to assess hypoxic and tumour burden respectively and correlated with fMRI sequences.Integrated design: fMRI and molecular samples are collected during chemoradiotherapy with limited additional appointments or effort required for enrolled patients, allowing for smooth translation of imaging and biopsy protocol into wider clinical practice.Single-site study: Patient recruitment is limited to eligible patients referred for chemoradiotherapy at a single cancer centre.

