This has been clarified in a systematic review, which details prospective studies using different fMRI techniques in cervical cancer. DWI and DCE-MRI represent the most used techniques, followed by BOLD-MRI. Furthermore, the majority of studies evaluated a single technique rather than a combination. This has led to a lack of consensus confounded by ‘multiple interacting factors, including histology, grade, hypoxia, vascularity and cellularity that can influence fMRI-derived parameters’. To account for this, future studies will need to employ combinations of fMRI techniques to generate ‘a more holistic assessment of the tumour, simultaneously assessing multiple tumour features to improve outcome prediction. Refinement of fMRI as a predictive and prognostic marker can be improved further by combining clinicopathological scoring and or genomic signatures for hypoxia.^6^

In addition to a multiparametric approach, fMRI needs to be repeated across treatment to discern tumour response and relate it to fMRI-derived parameters. Spatial data can also be acquired—an example of which DCE-MRI can identify a ‘functional risk volume’ within the tumour associated with poorer response to treatment. Tumours with a ‘functional risk volume’ displayed poor vascularity and tumour permeability.^7^ More recently, a study demonstrated combining DWI-derived and DCE-derived parameters to describe the ‘hypoxic fraction’ of cervical tumours linking this to disease-free survival.^8^

The Exploratory study of using Magnetic resonance Prognostic Imaging markers for Radiotherapy In Cervix cancer (EMPIRIC) study aims to build on previous studies and address the gaps in the current evidence base by performing multiparametric fMRI (DWI, DCE and BOLD-MRI) across treatment in patients with cervical cancer, alongside collection of blood samples for circulating tumour cell (CTC) and circulating tumour DNA (CtDNA) and tissue biopsies to facilitate parallel molecular analysis. This holistic approach to tumour characterisation will provide the tools to generate a meaningful predictive and prognostic model for personalised radiotherapy for cervical cancer.

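### Each temporal change in an fMRI parameter is tested without its pre-CRT value, so its reported OR can reflect baseline, and no planned analysis asks whether a repeat scan adds to the first

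*Protocol article*

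**What the plan says.** The Statistical analysis section lists the predictors of progression-free survival, overall survival, tumour volume reduction and tissue marker change as "Different thresholds and temporal changes of fMRI parameters (DCE-MRI, DWI-MRI and BOLD-MRI) at various time points during cervical CRT". Every analysis begins with a one-predictor logistic model, reported as an OR with 95% CI and a likelihood-ratio p value. Covariates "with a p<0.1 will be entered into a multivariate, forward conditional logistic regression", and significance is then judged at p<0.05. No variable is forced into any model.

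The wording lets a parameter's pre-CRT value and its value at fraction 10 or 25 be candidates in their own right, alongside the change. It does not require the pre-CRT value to be present when its change is assessed.

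Repeat scanning is central to the study's rationale. The Introduction argues that "fMRI needs to be repeated across treatment to discern tumour response and relate it to fMRI-derived parameters", and the strengths and limitations box says that the three scans "will capture longitudinal changes in tumour and fMRI-derived parameters".

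**The concern.** A change computed as the later value minus the earlier one carries the earlier value with a negative sign. Tested alone, its OR mixes the effect of the change with the effect of where the tumour started. If only the pre-CRT value is prognostic, the change can still look prognostic, and the plan requires that univariate OR and p value to be reported.

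The natural question for a three-scan schedule is whether the fraction 10 or fraction 25 scan tells us anything about outcome that the planning scan did not. No listed analysis asks this. Forward selection answers it only by accident, when the pre-CRT value happens to be selected first and the change is then tested against it. The Future work section plans a validation study and then a randomised dose-escalation study built on the resulting model. A statement that on-treatment change predicts outcome, when the pre-CRT scan carries all the information, would therefore mislead later design.

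**Working it through.** **The plan's own figures.** From Sample size and power:
- Accrual: 30 patients a year × (1 − 0.30) = 21 a year, and 2 × 21 = 42 over 24 months, against a target of 40.
- Events: 40 × 0.35 = 14.

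All of these reproduce. No effect size or power is stated.

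**Algebra.** Let B be the pre-CRT value, F the on-treatment value and C = F − B. Assume equal variances σ² and correlation ρ between B and F.
- cov(B, C) = ρσ² − σ² = −(1 − ρ)σ²
- var(C) = 2(1 − ρ)σ²
- corr(B, C) = −(1 − ρ)/√(2(1 − ρ)) = −√((1 − ρ)/2)

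For ρ = 0.3, 0.5 and 0.7 this is −√0.35 = −0.59, −√0.25 = −0.50 and −√0.15 = −0.39.

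**Simulation.** The documents give n = 40, the 35% event rate, the p<0.1 gate and the p<0.05 criterion. The assumptions are normal B and F with equal SD, ρ of 0.3 to 0.7, and ORs of 2 to 3 per SD. Tests are logistic likelihood-ratio tests. With about 2,000 runs per setting, results move by a point or two between repeats.

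*Only baseline matters:*

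| Quantity | Share of studies |
|---|---|
| Change alone, p<0.1 (ρ = 0.3/0.5/0.7), OR 2 | 32/26/19% |
| Same, OR 3 | 51/41/29% |
| Change alone, p<0.1, no effect of anything | about 11% |
| Change alone, p<0.05 | about 12-40% |
| Change given baseline, p<0.05 | 5-8% |
| Final model, candidates B and C: change retained | 5-9% (4-5% with no effect) |
| Final model, candidates B, F and C: F or C retained | about 13-18% |

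Part of the last row is ordinary chance. Two on-treatment terms are on offer, so up to about 2 × 5% = 10% could be retained with no effect at all.

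*Baseline and change both matter, in the same direction.* With B, F and C as candidates, an on-treatment term (F or C) is in the final model in 44-87% of studies. The test of change given baseline reaches p<0.05 in 38-75%. The reason is simple: at ρ = 0.5 the SD of C is 1, and log 3·B + log 3·C = log 3·F, so this is exactly an effect of the on-treatment value, which is itself a candidate.

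*Only change matters (no baseline effect once change is known).* Change passes p<0.1 alone in 76/63/47% at ρ = 0.3/0.5/0.7, against 59/52/43% with baseline in the model.

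**The case against.** A reader might go further and infer that the p<0.1 screen throws away genuine on-treatment effects. Change alone does pass less often when the on-treatment value drives outcome: at OR 2, 32/28/19% alone against 59/55/42% with baseline in the model. But that comparison leaves out the raw on-treatment value, which the Statistical analysis section also allows as a candidate. With it included, the written plan detects an on-treatment signal at least as often as the adjusted test. When change alone carries the signal, the unadjusted screen does better. The documents therefore do not support a general loss of real effects. Replacing the screen, or dropping the raw fraction 10 and 25 values, would lower detection.

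A reader might also carry the 12-40% into the final model. That is not supported either. Significance is declared after the multivariable step, where baseline competes if it is a candidate, and the figure there is about 13-18%.

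The linear dependence among B, F and C does little harm to prediction, since any two of the three give the same fitted model and AUC. It only means that the form selected cannot be read as showing whether level or change matters.

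The article does not define change as a difference; a percentage or ratio is possible, and that detail may properly sit in an analysis plan. The formula and the sizes above would then differ. What stands is that testing each predictor alone first, with no baseline term required, is fixed in the text and not left to a later document.

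**Conclusion.** The concern holds in a limited form. The plan reports ORs for change that are not adjusted for baseline, and it has no analysis of whether a repeat scan adds to the pre-CRT scan. With a baseline-only effect, change alone is nominally significant in about 12-40% of studies against 5-8% when baseline is in the model. The plan's own selection step reduces the misattribution to about 13-18%, part of it chance, provided that the pre-CRT value is among the candidates. The text permits that but does not guarantee it.

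Under the raw-difference, equal-variance assumption, the dependence of change on baseline follows from the algebra. The sizes depend on the assumed correlations and ORs, none of which the documents give. The study is exploratory and "The proposed sample size of 40 patients is a convenience-based sampling", so this is a matter of what may be claimed from the repeat scans and does not invalidate the planned analyses.

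**What to change.** Keep the planned univariate analyses and keep the raw on-treatment values as candidates. Add to the Statistical analysis section, for a short pre-specified list of parameters:

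- Model 1: the pre-CRT value.
- Model 2: the pre-CRT value plus the change to fraction 10; and, as a separate comparison, the pre-CRT value plus the change to fraction 25.
- The pre-CRT term is exempt from the p<0.1 gate in these models.
- Report the adjusted OR for change with 95% CI, the likelihood-ratio p value for adding it, and the gain in AUC.
- Base any claim that repeat scanning adds prognostic information on this comparison, and label univariate ORs for change as not adjusted for baseline.

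The cost is analysis time and one extra degree of freedom per test; no new scans or data are needed. Precision is the real limit. The plan says that "a 2-year recurrence rate (local, nodal and distant) of 35% is assumed resulting in an estimated number of 14 events", so a two-term model has 14/2 = 7 events per term. Only a few parameters should be listed, and they should be chosen before outcome data are examined.
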